#### Waiting list control group

From the waiting list control group we establish risk profiles, lifestyle assessment, health status, work status and absence from work at baseline and again at the start of PPA CMR one year later. At the start of PPA CMR newly detected patients with CMD will be established, based on ICPC-1-coded diagnoses in the EMRs. Patients who develop a new CMD - documented through an ICPC-1-coded diagnoses in the EMR - will not be eligible for participation in PPA CMR, but will receive questionnaires for follow-up. When the waiting list control group starts with the intervention phase, the patients follow the identical route as the intervention group (see Figure 2).

### Analyses and statistical methods

We will analyze the data from this study according to the intention-to-treat principle. Analyses will be performed with all data available. Since the availability of data will depend on the response rate, a fully complete dataset cannot be expected. Multiple imputation techniques are used for handling missing data.

#### Sample size calculation

Calculation of the sample size is based on the reduction of smokers in the intervention group after one year follow-up, one of the primary outcome measures. The smoking prevalence in the Netherlands is 25% [35]. We expect a reduction in smoking prevalence from 25% to 20% after one year treatment and a stable number of smokers in the waiting list control group. In order to achieve this reduction, 721 patients are needed in the intervention group. This calculation is based on an alpha of 0.05 (two-sided), a power of beta = 0.80 and a ratio intervention group versus control group of 1:4). The 1:4 ratio represents a fair comparison between the intervention and the large control group. Based on the pilot implementation study of the PC, we expect approximately 21 patients per practice in the intervention group after twelve months follow -up [14,15]. A low response rate has been taken into account with this estimate. This would result in the inclusion of 721/21 = 34 general practices. However, in this study patients are clustered within general practices and an oversampling of 15% is needed to correct for this clustering in multi-level analyses. Therefore, we need approximately 40 general practices. The number of participants and practices will result in sufficient power to establish statistically significant differences between other subgroups.

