### Randomization

Eligible patients are randomized within each general practice into four time groups: two intervention groups and two waiting list control groups. We will use the statistical software program Stata version 12 for the randomization. Every four months a new group starts with the intervention, starting with the two intervention groups. After twelve months the two waiting list control groups will sequentially start with PPA CMR.

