### Non-response analyses

The results of the non-response analyses of the INTEGRATE study will provide more information about the characteristics and motives of non-participants in PPA CMR. This knowledge is relevant and essential for the development and evaluation of participation enhancing strategies. The INTEGRATE study has a unique design where the results of the non-response analyses, performed at an early time point during the study, can be used as input for developing interventions to increase the participation rate later in the study. Effective participation enhancing strategies are useful when optimizing implementation of future prevention programs in primary care.

In comparable studies, including the pilot implementation of PC [14,15] the response rates were low, ranging from 3% to 75% [14,15,18]. Since this has been taken into account in the sample size calculation, sufficient power is expected even with low response rates. To enhance participation rates we plan to use several strategies, based on advise and results of previous studies [14] and on non-response analyses during the study. The accompanying information letter will emphasize safety in handling privacy sensitive data, especially digital data. Furthermore, the information letter will contain a short recap of the purpose of the letter and the advice to ask a family member for help with translation if considered necessary. The letter will present the recap in different languages. Reminder letters with a paper version of the risk estimation will be sent to all non-responders after two weeks. Furthermore, we evaluate a subgroup that is offered the possibility to bypass one of the GP consultations by ordering a toolbox. The toolbox is a tool that stimulates self-management; patients are able to take more responsibility for their own health. Furthermore, obtaining the additional measurements through a toolbox is easier to incorporate into ones busy life and this might enhance participation rates. A higher participation rate increases the cost-effectiveness of the entire program.

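### The 721 intervention patients depend on a 1:4 intervention-to-control ratio that the two-plus-two randomisation, as described, does not deliver, so the 80% power must be restated

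*Protocol article*

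**What the plan says.** All of the following is in the Protocol article.

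- **Sample size calculation.** The calculation uses smoking, one of the primary outcome measures: "We expect a reduction in smoking prevalence from 25% to 20% after one year treatment and a stable number of smokers in the waiting list" (the comparison arm). The error rate is given as "This calculation is based on an alpha of 0.05 (two-sided", and the remaining inputs as "a power of beta = 0.80 and a ratio intervention group versus control group of 1:4". The result is 721 intervention patients. At 21 per practice this becomes 34 practices, and a 15% allowance for clustering raises it to about 40. The only reason given for the ratio is: "The 1:4 ratio represents a fair comparison between the intervention and the large control group".
- **Randomization.** "Eligible patients are randomized within each general practice into four time groups: two intervention groups and two waiting list control groups". Group sizes are not given.
- **Choices in study design.** Randomisation is of individuals, and all eligible patients are randomised at baseline, before consent.
- **Analyses and statistical methods; Effectiveness of PPA CMR.** The intervention group is compared with the waiting-list control group by intention to treat, with multilevel regression.

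Two further assurances draw on the same calculation. The Sample size section promises "sufficient power to establish statistically significant differences between other subgroups". The Non-response analyses section says: "Since this has been taken into account in the sample size calculation, sufficient power is expected even with low response rates".

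**The concern.** The ratio in the sample size calculation and the allocation in the Randomization section describe different trials. Two groups against two groups is most naturally read as 1:1, and no section gives unequal sizes or any other route to four controls per intervention patient. The expected number of controls is never stated.

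The ratio matters because, for a fixed intervention arm, going from 1:1 to 1:4 accounts for much of the claimed power. Smoking is the only endpoint with a sample size basis. If the analysed arms turn out nearly equal, a null result would be read as coming from a trial with 80% power when the true figure may be well below that. If 1:4 is instead reached because far more controls than intervention patients enter the analysis, power is kept but the groups compared are no longer the groups randomised.

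**Working it through.** **Inputs.** From Sample size calculation: p1 = 0.20 (intervention), p2 = 0.25 (control), two-sided alpha 0.05 (z = 1.960), power 0.80 (z = 0.842; the article writes this as beta, a slip of wording), k = 4 controls per intervention patient, 21 intervention patients per practice, 15% clustering allowance. From Study population: about 28,500 eligible patients. About 40 practices.

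**Reproducing 721.** With p̄ = (p1 + k·p2)/(1 + k),

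n = [1.960·√(p̄(1−p̄)(1+1/k)) + 0.842·√(p1(1−p1) + p2(1−p2)/k)]² / (p1−p2)²

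At k = 4, p̄ = 0.24 and n = (0.9359 + 0.3828)²/0.0025 = 695.6. The continuity correction, n/4·[1 + √(1 + 2(k+1)/(n·k·0.05))]², gives 720.3, which rounds up to **721**. The matching control arm is 4 × 721 = 2,884.

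**The same formula at 1:1.** At k = 1, p̄ = 0.225 and n = (1.1575 + 0.4961)²/0.0025 = 1,093.7, so 1,094 per arm (1,134 with continuity correction).

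**Power by ratio.** Power = Φ[(0.05 − 1.960·SE0)/SE1], where SE0 is the pooled and SE1 the unpooled standard error. The corrected version first subtracts 0.5(1/n1 + 1/n2) from 0.05. Example, 721 per arm: SE0 = 0.02199, SE1 = 0.02195, z = 0.314, power 62.3%.

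| Intervention patients | 1:1 | 1:2 | 1:4 |
|---|---|---|---|
| 721 | 62.3% (59.9%) | 74.2% (72.4%) | 81.4% (80.0%) |
| 840/1.15 = 730 | 62.9% (60.5%) | 74.8% (73.0%) | 81.9% (80.6%) |
| 840 (40 × 21, clustering ignored) | 69.0% (66.9%) | 80.5% (79.1%) | 87.0% (86.0%) |

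Figures in brackets are continuity-corrected. All are for an unadjusted comparison of two proportions.

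**Detectable difference.** With 840 per arm and clustering ignored, 25% v 19.3% has 80.4% power uncorrected (78.7% corrected).

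**What 1:4 would require under equal randomisation.** 28,500/40 = 712.5 eligible patients per practice, or 356 per arm. The article expects 21 intervention patients per practice; 1:4 then means 84 controls. That is 21/356 = 5.9% of those randomised to intervention against 84/356 = 23.6% of those randomised to control.

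**The case against.** The strongest case on the other side has four parts.

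1. *Group sizes are not stated, and the article speaks of a large control group.* The authors may have intended unequal groups, or expected controls, who at first only complete a questionnaire, to respond more. This stands to the extent that 1:1 is an assumption. It does not remove the gap: neither mechanism is written down, and the second would come from differential participation rather than from randomisation. The article itself warns, under Choices in study design, that randomising before consent can induce selective response.

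2. *The 21 per practice is a forecast.* It is based on the pilot and already allows for low response. At 1:1 in 40 practices, 80% power needs 1,094/40 to 1,134/40 = 27-28 intervention patients per practice (7.7-8.0% of 356), or 31-33 (8.8-9.2%) with the 15% allowance. If 21 counts only patients late in the pathway, the full intention-to-treat arm could be larger. This stands: a modest rise in yield would restore the power.

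3. *The planned analysis is a multivariable regression on change.* If it adjusts for baseline smoking, it will be more efficient than the comparison used here. As a rough approximation (variance scaled by 1 − r²; r is assumed, since the article gives none), 840 per arm reaches 80% when 1 − r² = 840/1,094 to 840/1,134, that is r about 0.48-0.51. This also stands, but the article's own calculation is unadjusted, and the like-for-like check on it must be too.

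4. *The low-response sentence refers back to the 21 per practice.* It does not promise power at the bottom of the 3% to 75% range of response rates cited beside it. That is fair, so the sentence needs a condition rather than a rebuttal.

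A reader might infer that the trial's power simply is 60-69%, or that more practices are required. The documents support neither: both need equal groups, equal yield, exactly 21 per practice and an unadjusted analysis, and the article fixes only the third, as an expectation.

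**Conclusion.** The inconsistency is real and survives every objection. The 721 holds only at 1:4, and the described randomisation does not produce 1:4.

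The size of the shortfall is conditional. With equal groups and similar 12-month yield, unadjusted power is about 60-63% once clustering is allowed for and at most 67-69% if all 840 per arm count in full, against the stated 80%. At 1:2 it is 72-75% at 721-730 intervention patients and 79-81% at 840 with clustering ignored, so at that ratio most of the loss disappears.

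The remaining route to the stated power, equal randomisation with about 24% of controls and 6% of intervention patients analysed, would not be a like-for-like intention-to-treat comparison. The general assurance about other subgroups has no calculation behind it. The low-response assurance holds only as far as the 21-per-practice yield and the ratio hold.

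**What to change.** - In Randomization and Sample size calculation, state the sizes of the four groups and the number expected at 12 months in each arm.
- Define the analysed population by the same responder and risk filter in both arms. This is feasible: the Control group section shows that controls answer the risk estimation items at baseline.
- Restate the power or the detectable difference at the ratio this gives, naming the assumptions. For example: if groups are equal and yield is similar, 840 per arm gives about 67-69% power for 25% v 20%, or 80% for about 25% v 19.3%, unadjusted and before clustering. If unequal allocation is intended, write it into the Randomization section instead.
- Remove or qualify the sentence on power for other subgroups, and make the low-response sentence conditional on 21 intervention patients per practice.

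This is a change of wording. It asks for no extra patients or practices; the cost is a stated power that is likely to be less favourable.

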#### Effectiveness of PPA CMR

We will use multivariable multilevel regression analyses to study the effects of PPA CMR on change in individual risk factors and lifestyle and on the incidence of CMD after one year follow-up. Therefore, we compare the intervention group with the waiting list control group. In addition we will evaluate the influence of different response enhancing strategies on the effectiveness of PPA CMR. We will use linear or logistic regression for continuous or dichotomous data, respectively. Multilevel analysis is needed to correct for clustering of patients within practices.

#### Cost-effectiveness of PPA CMR

We will perform an economic evaluation to relate net incremental costs and effects of PPA CMR compared to the waiting list control group. Estimated costs are based on the healthcare and non-healthcare costs. After one year of follow-up, cost-effectiveness of PPA CMR will be established. To evaluate cost-effectiveness in the long term, modeling is required. We will use the RIVM-Chronic Disease Model (RIVM-CDM) to perform this long-term economic evaluation. The RIVM-CDM is a Markov-type, dynamic population-based model [28,29] and is able to relate changes in prevalence of risk factors to changes in future incidence of CMD. The model also contains data on costs of cardiovascular events and associated losses in quality of life. This model has extensively been used for the evaluation of cost-effectiveness of prevention programs targeted at lifestyle improvement [34,36-38].

The cost-effectiveness will be calculated per level of change in individual risk factors. Incremental cost-effectiveness ratios (ICER) are derived from calculating the net costs of PPA CMR compared to the waiting list control group, divided by its effect. In addition, we will calculate the incremental cost-utility ratios (ICUR). Therefore, the incremental costs of PPA CMR compared to the waiting list control group will be divided by the effects in quality adjusted life years (QALY’s) gained. Utility values as incorporated in the RIVM-CDM will be used for future cardiovascular events. Probabilistic sensitivity analysis are performed for all calculations.

#### Determinants of participation and compliance

The number of participants during the different phases of PPA CMR will be presented with frequency tables. Differences between participants and non-participants regarding age, gender, SES, ethnic background, and cardiometabolic risk are determined using univariable analysis (*t*-test, chi-square test). We will use descriptive statistics and multivariable regression analyses to determine the profile of participants and non-participants in PPA CMR.

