### Study population

The study will be conducted in approximately 40 general practices in the Netherlands, a representative sample of all Dutch general practices with regard to the distribution in rural/urban and solo/group practices. Inclusion and exclusion criteria for practices and patients are shown in Table 1.

**Table 1 T1:** Inclusion and exclusion criteria for practices and participants

	**Inclusion**	**Exclusion**
**General practices**	• Use of common Electronic Medical Record (EMR) system, in which electronic data extraction is possible	• Recently performed screening for patients at risk for cardio-metabolic disease
**Patients**	• Age between 45 and 70 years	• Receiving antihypertensive or lipid-lowering treatment
		• One of the following ICPC-I-codes: K74: Angina pectoris, K75: Acute myocardial infarction, K76: Other chronic ischaemic heart disease, K77: Heart failure, K86: Uncomplicated hypertension, K87: Hypertension with secondary organ damage, K89: Transient cerebral ischemia, K90: Stroke/cerebrovascular accident, K91: Atherosclerosis, K92: Peripheral vascular diseases, T90: Diabetes mellitus, T93: Lipid metabolism disorder

Inclusion criterion for practices:

•The use of an Electronic Medical Record (EMR) system, from which electronic data extraction is possible, covering approximately 90% of all Dutch general practices.

Exclusion criterion for practices:

•Previously performed systematic CMD screening of the entire or a non-random sample of the practice population.

All eligible patients of the included practices (approximately 28.500 patients) receive an invitation letter from their GP to participate in the INTEGRATE study.

Inclusion criterion for patients:

•Age between 45 and 70 years, which is according to the guideline of the Dutch College of GPs [13].

Exclusion criteria for patients:

•Previous diagnosis of CMD according to EMR (see Table 1 for list of International Classification of Primary Care (ICPC-1)-coded diagnoses [23]).

•Receiving antihypertensive and/or lipid-lowering treatment.

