### Endpoints and measurements

The endpoints of the INTEGRATE study are shown in Table 2. An overview of all measurements is shown in Figure 2.

**Table 2 T2:** Primary and secondary endpoints

**Primary endpoints**	**Secondary endpoints**
1. The number of newly detected patients with a CMD in one year follow-up	1. Difference in primary outcome 5 after implementation of different response-enhancing strategies
2. Change in individual risk factors (smoking, physical inactivity, obesity, unhealthy diet, blood pressure and cholesterol levels) for CMD between baseline and one year follow-up	2. Change in willingness to change lifestyle between baseline and one year follow-up
3. The expected number of newly detected patients with CMD and mortality after 5, 10,20 years and lifetime	3. Change in health status between baseline and one year follow up
4. Costs-effectiveness of PPA CMR	
5. Non-participation and compliance in different stages of PPA CMR	

For our secondary endpoints we will use the information provided for our primary endpoints.

1. *Newly detected patients with CMD at baseline and one year follow-up*

The number of newly detected patients with pre-existing CMD will be established after the second consultation and after one year follow-up, based on ICPC-1-coded diagnoses (see Table 1) in the EMRs.

2. *Change in individual risk factors for CMD between baseline and one year follow-up*

For patients with an increased risk for CMD, risk and lifestyle profiles will be established at the start of PPA CMR and after twelve months of follow-up. Risk profiles consist of the completed risk profile including the additional measurements done by the GP or with the self-management toolbox. The questions of the online risk estimation and lifestyle assessment are repeated after six months as well (see Figure 2).

For patients with a low risk for CMD we will establish risk and lifestyle profiles at the start of PPA CMR and after twelve months of follow-up. These risk profiles do not contain the additional measurements.

3. *Expected newly detected patients with CMD and mortality after 5, 10, 20 years and lifetime*

We will use the RIVM-Chronic Disease Model (RIVM-CDM) [28,29] to extrapolate the number of possible prevented CMD due to PPA CMR with a time horizon of 5, 10 and 20 years. The calculations are based on changes in risk profile during one year of treatment.

4. *Costs-effectiveness of PPA CMR*

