Information on determinants of non-participation and successful completion of PPA CMR is used to study the differences in characteristics of responders and non-responders. We will also study differences in characteristics of participating practices (e.g. urban/rural locations, solo/group practices, organization of lifestyle interventions) to find practice-related factors that are associated with participation and compliance rates. The analyses of determinants for participation shall be performed in the first groups starting with the intervention. Depending on the findings, response-enhancing strategies are developed and implemented in the waiting list control groups that subsequently enter the study. Data collection for subgroups receiving a response enhancing intervention is done in the same way as described above.

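### The determinants analysis for primary endpoint 5 does not carry over the practice-level correction that the article requires for effectiveness, although practice-related factors are among the determinants to be studied

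*Protocol article*

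**What the plan says.** Table 2 of the protocol article lists "Non-participation and compliance in different stages of PPA CMR" as primary endpoint 5. Its only analysis section is Determinants of participation and compliance. That section states: "Differences between participants and non-participants regarding age, gender, SES, ethnic background, and cardiometabolic risk are determined using univariable analysis", naming the t-test and chi-square test. It continues: "We will use descriptive statistics and multivariable regression analyses to determine the profile of participants and non-participants in PPA CMR". Neither sentence mentions practices.

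The section Effectiveness of PPA CMR reads differently: "We will use multivariable multilevel regression analyses to study the effects of PPA CMR on change in individual risk factors". It closes with the reason: "Multilevel analysis is needed to correct for clustering of patients within practices". The sample size section also adds 15% for clustering.

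Under Endpoints and measurements (endpoint 5), characteristics of the practices themselves (urban or rural, solo or group, how lifestyle interventions are organised) are to be compared "to find practice-related factors that are associated with participation and compliance rates". No test is named for these factors. On timing, the same section says: "The analyses of determinants for participation shall be performed in the first groups starting with the intervention". Depending on the findings, response-enhancing strategies are then developed for the waiting-list groups.

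**The concern.** The article accepts that patients within a practice are correlated and corrects for this in one analysis of a primary endpoint, but not in another. The omission falls where clustering can do more harm. Patients are randomised individually within practices, so the treatment comparison is largely within practice. A practice characteristic is a purely between-practice comparison with about 40 independent units. A test that counts each patient as an independent observation of such a characteristic gives standard errors that are too small.

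SES and ethnic background may also differ between practices, so tests on them could be affected to a lesser degree. What is at stake is the credibility of the reported determinants. They feed the choice of response-enhancing strategies during the study and the advice on later implementation.

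**Working it through.** **Reproducing the plan's own figures.** Smoking 20% versus 25%, two-sided alpha 0.05, power 80%, ratio 1:4, with continuity correction, gives 721 in the intervention group, as stated. Then 721/21 = 34.3 practices, and 34 × 1.15 = 39.1, so about 40. These figures are not affected by this point. The article gives no ICC, power or error rate for the determinants analysis.

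**Inputs.**
- Invited patients: "All eligible patients of the included practices (approximately 28.500 patients) receive an invitation letter from their GP" (Study population).
- Practices: about 40 (Sample size calculation).
- Four randomised groups, two of them intervention groups (Randomization). Equal group sizes are assumed.
- ICC: 15% inflation at 21 patients per practice implies 0.15/(21 − 1) = 0.0075. This comes from the smoking calculation; its use for participation is an assumption.
- ICCs of 0.001, 0.02 and 0.05 are further assumptions that show the range.

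**Cluster size.** Both intervention groups: 28,500/40/2 = 356 per practice. One starting group: 28,500/40/4 = 178. Compliance: 21 per practice, the article's expectation for the intervention group at twelve months.

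**Practice-level factor tested without a practice level.** Design effect DE = 1 + (m − 1) × ICC. Actual error of a nominal 5% test = 2 × [1 − Φ(1.96/√DE)].

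| Patients per practice (m) | ICC | DE | Actual type I error |
|---|---|---|---|
| 356 | 0.0075 | 3.66 | 31% |
| 356 | 0.001 | 1.36 | 9% |
| 356 | 0.02 | 8.11 | 49% |
| 356 | 0.05 | 18.76 | 65% |
| 178 | 0.0075 | 2.33 | 20% |
| 21 | 0.0075 | 1.15 | 7% |

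At DE 3.66 the standard error is too small by a factor of √3.66 = 1.9.

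**Patient-level factor.** If the factor has its own between-practice correlation ICC_x, then DE = 1 + (m − 1) × ICC × ICC_x. With ICC_x = 0 (gender, for example), DE = 1 and the error stays at 5%. With an assumed ICC_x of 0.10 for SES or ethnic background, m = 356 and ICC 0.0075, DE = 1 + 355 × 0.00075 = 1.27 and the error is about 8%.

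**Simulation check.** 40 practices of 356 patients, an assumed 33% participation, no true effect, 2,000 runs per ICC:

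| ICC | Practice factor, no practice level | Practice factor, practice-level analysis | Unclustered patient factor | Clustered patient factor (ICC_x 0.10) |
|---|---|---|---|---|
| 0.0075 | 31% | 6% | 4% | 8% |
| 0.02 | 50% | 5% | 5% | 13% |
| 0.05 | 64% | 4% | 5% | 23% |

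The simulation agrees with the formulas. Analysing the practice factor at practice level brings its error back to about the nominal rate.

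**The case against.** The strongest reply is that the article never assigns the t-test or chi-square test to a practice characteristic. The sentence naming them lists five patient characteristics, and the sentence on practice-related factors names no test. A reader might infer that the stated tests will make practice factors significant far too often. The text does not show that, and the 31% applies only if those factors are in fact tested without a practice level.

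Nor does the article call its regression single-level. That reading rests on the absence of the word multilevel, and the closing sentence of the effectiveness section could be taken as a general principle, although it stands under that heading. An article may also leave model detail to an analysis plan. All of this stands as a limit on the point. But the determinants section does name methods, and two of them, the t-test and chi-square test, assume independent patients, so this is more than silence.

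The numbers rest on a borrowed ICC. This also stands, and it is why a range is given.

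Finally, a reader might infer that false determinants would bias the main comparison. They would not: the strategies are used only when the waiting-list groups receive the intervention, after their control year. The choice of strategies also draws on stated reasons for non-participation, attitudes towards strategies and previous studies, and the effect of the strategies is assessed separately as secondary endpoint 1.

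**Conclusion.** The point holds as an inconsistency that should be corrected. The analysis section for primary endpoint 5 does not carry over a correction that the same article calls necessary, while practice-related factors are among the determinants it plans to study.

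The size is conditional. For a practice factor tested without a practice level, the nominal 5% becomes about 31% at 356 patients per practice and ICC 0.0075. Every scenario calculated for such a factor exceeds 5%, but by widely differing amounts: compliance at 21 per practice is barely affected, and the large-cluster participation analysis much more so. For the listed patient characteristics the consequence is nil to modest, unless both participation and the characteristic cluster clearly by practice. The documents give no ICC for participation and none for SES or ethnic background, so no single figure can be claimed.

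**What to change.** In Determinants of participation and compliance, specify multilevel logistic regression with participation (or compliance) as the outcome and a random intercept for practice, for both the univariable and the multivariable analyses. State that practice-level factors are tested against between-practice variation, with about 40 − 2 = 38 degrees of freedom for a two-category factor. The simple comparison tables can stay as description.

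This needs no new data, and the class of model is already planned for effectiveness. The price is wider intervals for practice factors and for patient factors that cluster by practice. With about 40 practices, some practice-related associations may then be too imprecise to establish.
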